### Sample size

Based on a previous clinical trial, the effective rate of berberine, a famous Chinese medicine, in the prevention of CRA recurrence was 11% (Chen et al., 2020). The estimated effective rate of SJZD is 20% in this study. Following the 1:1 parallel control principle, SAS statistical analysis software was used to generate the sample size with a double-sided significance level of 0.05 and a power of 80% (α = 0.05, β = 0.2). Assuming that the dropout rate in each group was 10%, a requirement of 240 cases was determined (*n* = 120 in each group).

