### Outcomes

The primary outcome is the recurrence rate of CRA between the SJZD group and the placebo group at the first year after CRA removal. The number, size and location of adenomas will be recorded. Pathological type will also be recorded if recurrent adenomas meet the criteria for resection. Secondary outcomes include the following: 1) the recurrence rate of CRA at the second year post-polypectomy; 2) the pathological type of adenoma detected at either of the two endoscopies; and 3) the changes in spleen deficiency PRO scores after intervention.

Safety outcomes will comprise physical examinations, vital signs and laboratory examinations at every visit and AEs during the intervention phase. Laboratory indices will include routine blood tests, routine urine tests, routine stool tests, liver function tests, renal function tests and electrocardiograms. In the event of AEs, the onset time, symptoms and signs, duration of event and abnormal laboratory indicators or imaging results will be recorded. The definition and grade assessment of AEs are in accordance with the National Cancer Institute Common Terminology Criteria for Adverse Events (Version 5.0) (SERVICES USDOHAH, 2017).

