## Discussion

Colorectal cancer is a major health concern globally, with the age-standardized incidence and mortality rate reaching 26.7 and 13.7 per 100,000 population, respectively (Kocarnik et al., 2019). The escalation of colorectal cancers worldwide has prompted clinicians to focus on endoscopic screening, adenoma resection and periodic surveillance after removal to prevent the subsequent development of carcinoma. CRAs, one of the most common precancerous lesions of colorectal cancers, have a relatively high recurrence rate. Previous studies have reported CRAs recurrence rates ranging from 26.6% (Pommergaard et al., 2016) to 51.6% (Higurashi et al., 2016; Chen et al., 2020) after polypectomy, with an observed trend of increased recurrence rates over longer follow-up durations (Gao et al., 2010). Additionally, various factors can influence CRA recurrence rates. While factors such as sex, gene mutations and family history are unmodifiable, endoscopic procedures, diet and chemoprevention agents are modifiable (Hao et al., 2020).

Over the past decades, many studies have explored the potential of certain drugs or nutritional agents in reducing CRA recurrence. A prospective study reported a significant association between higher total vitamin D intake and a reduced risk of conventional adenoma, regardless of the high or low risk of adenomas (Kim et al., 2021). However, this study only recruited young female participants, and extrapolating this result to the general population should be approached cautiously. In a comparative analysis of two RCTs, the Vitamin D/Calcium Polyp Prevention Study (VCPPS, 2004–2013) (Baron et al., 2015) and the Calcium Polyp Prevention Study (CPPS, 1988–1996) (Baron et al., 1999), showed that the protective effect of calcium supplementation on lowering the risk of recurrent CRAs was attenuated by an abnormally high body mass index (Barry et al., 2019). This finding limits the widespread usage of calcium in all patients with CRAs. Recently, a high-quality clinical study reported that berberine, a drug derived from traditional Chinese herbal medicine, effectively reduced the recurrence rate of adenomas after polypectomy (Chen et al., 2020), indicating the promising role of Chinese herbal medicine in the prevention of recurrent CRAs.

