SJZD, a renowned prescription in treating SDS over hundreds of years in China, has long been extensively used in gastrointestinal diseases and is favored by clinicians because it can be modified by adding other Chinese herbs under various pathological conditions. To better understand the mechanism of SJZD, the chemical substances of this decoction have been identified (Guan et al., 2018), and the pharmaceutical mechanism of the herbs was also explored with the aid of modern methodology. Studies have found that ginsenoside Rb2, an active substance of ginseng, has an inhibitory effect on the migration, invasion and metastasis of colorectal cancer cells (Dai et al., 2019c). Furthermore, researchers found that non-polysaccharide NPS and polysaccharide S-3, two effective components of SJZD, could stimulate intestinal peristalsis and regulate the immune environment of the intestine in a rat model with SDS (Ma et al., 2021). Other modified decoctions and derivatives of SJZD components have been proven to be effective in treating functional dyspepsia (Lv et al., 2017) and chronic atrophic gastritis (Tian et al., 2019), reducing liver metastasis in a rat model with colon cancer (Zhou et al., 2019), improving gastric movement by restoring the mitochondrial quality control system (Zhang et al., 2022), and inducing apoptosis of colorectal cancer cells (Li et al., 2020). However, the therapeutic effect of SJZD in CRA recurrence is still unknown. Therefore, this trial is designed to explore the efficacy and safety of SJZD in the prevention and treatment of SDS patients after CRA removal.

There are some limitations in this study. First, as there is no reduction or escalation in drug dose, the dose‒response effect will not be compared. Second, the intervention phase is only 12 months, and the follow-up duration is 24 months. A very long-term observation for CRA recurrence will not be completed. Third, the participating sites are all located in Shanghai, and a larger sample size is needed in the future.

In summary, this trial aims to investigate the role of SJZD in patients with SDS after CRA polypectomy. Under the guidance of TCM, we hope to accumulate more experience for clinical practice and provide high-quality evidence of herbal medicine in coping with colorectal disease.

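### The printed sample-size inputs (11% and 20%) do not produce 240 patients and do not define the SJZD-versus-placebo recurrence comparison

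*Protocol article*

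**What the plan says.** Under Outcomes, the primary endpoint is binary and placebo-controlled: "The primary outcome is the recurrence rate of CRA between the SJZD group and the placebo group at the first year after CRA removal". Statistical analysis assigns it a chi-square test between the two groups.

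Sample size gives two rates. The first comes from a previous trial of another drug: "the effective rate of berberine, a famous Chinese medicine, in the prevention of CRA recurrence was 11" per cent. The second is the assumption for this trial: "The estimated effective rate of SJZD is 20% in this study". The calculation is two-group ("Following the 1:1 parallel control principle"), run in SAS "with a double-sided significance level of 0.05 and a power of 80" per cent. With 10% dropout per group, "a requirement of 240 cases was determined", 120 per group.

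The section does not say what an effective rate is and gives no expected recurrence rate for either arm. Background rates appear only in the Discussion ("Previous studies have reported CRAs recurrence rates ranging from 26.6" per cent, up to 51.6%) and are not linked to the calculation.

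**The concern.** A two-group sample size for a binary endpoint needs the event proportion expected in each group. Here one printed figure belongs to a drug that is not in the trial, and neither is described as a recurrence rate. A reader who enters the only two rates available gets more than twice the stated total.

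What is at stake is the reading of the primary result. The stated 80% power attaches to no identifiable hypothesis. If the comparison is not significant, nobody can say from this text which reduction in recurrence the trial had a good chance of detecting.

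**Working it through.** **Inputs.** From Sample size: rates 0.11 and 0.20, two-sided alpha 0.05 (z = 1.960), power 0.80 (z = 0.842), 1:1 allocation, 10% dropout, 240 in total. Evaluable per arm: 120 × 0.9 = 108. From the Discussion, as an assumed range only: control recurrence 26.6% to 51.6%.

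**Formula.** Per arm, with p̄ the mean of p1 and p2:

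n = [1.960·√(2p̄(1−p̄)) + 0.842·√(p1(1−p1)+p2(1−p2))]² / (p1−p2)²

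**Step 1: try to reproduce 240 from 11% and 20%.**
- p̄ = 0.155, so √(2 × 0.155 × 0.845) = 0.5118 and √(0.11×0.89 + 0.20×0.80) = 0.5078.
- n = (1.0031 + 0.4274)² / 0.09² = 252.6, so 253 per arm.
- Dropout: 506/0.9 = 562.2, about 562 in total, or 564 if each arm is rounded up to 282.
- Power at 108 per arm: Φ[(0.09·√108 − 1.0031)/0.5078] = Φ(−0.134) = 44.7%. With all 120 per arm evaluable it is about 49%.

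The stated 240 is not reproduced.

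**Step 2: vary the method, keeping 11% and 20%.** Totals including dropout as n/(1−0.10):

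| Variant | Total |
|---|---|
| Two-sided, pooled | 564 |
| Two-sided, continuity-corrected | 612 |
| Two-sided, unpooled | 556 |
| Two-sided, arcsine | 554 |
| One-sided, pooled | 444 |
| One-sided, continuity-corrected | 492 |

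The smallest variant tried (one-sided, unpooled or arcsine, dropout added as n × 1.10) still needs 217 per arm, 434 in total.

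**Step 3: read the 20% as a reduction against placebo.** Control rates are the assumed range above.

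| Reading | Control 26.6%: n per arm, power at 108 | Control 51.6%: n per arm, power at 108 |
|---|---|---|
| 20-point absolute reduction | 53.1, 98% | 94.2, 85% |
| 20% relative reduction | 1009, 15% | 366, 33% |

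For the absolute reading, the total with dropout is about 120 (54/0.9 = 60 per arm) to about 210 (2 × 94.2/0.9 = 209.2). With continuity correction, n is 62.7 to 103.9 per arm, giving 2 × 70 = 140 to 2 × 116 = 232.

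For the relative reading, 1122 to 407 per arm are needed with dropout.

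**Step 4: an effect of 11 points**, if the berberine figure is an absolute reduction. Power at 108 per arm is 51% (from 26.6%) to 37% (from 51.6%).

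**Step 5: what 108 per arm can detect.** Solving for 80% power gives a reduction of 14.9 points from 26.6%, 17.6 points from 40%, or 18.7 points from 51.6%.

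**The case against.** The best defence is that an effective rate in preventing recurrence can naturally mean an absolute reduction. Take 20 points off the protocol's own upper background rate, 51.6%, with continuity correction: 116 per arm, 232 in total. Rounding that up to 240 would be ordinary. Power at 108 evaluable per arm is then 85%, or about 82% with continuity correction, and both meet the stated 80%. An unstated control rate of 55% to 60% comes closer still, at 118 to 119 per arm. The article also condenses a fuller protocol, where the rates entered into SAS may be recorded.

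Much of this stands. A reader might infer from 562 and 45% that the trial is underpowered. The document does not support that: those figures are the power for a contrast of 11% with 20%, and the text never says that 11% is the placebo rate. Nor can one say that 240 is indefensible on every reading, since a 20-point absolute reduction from the cited background rates would be adequately covered.

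What does not stand is the sizing statement as printed. The article sets out a calculation with inputs and an output, and the inputs do not give the output. Every near match needs something the text does not supply: a control rate, a definition, a continuity correction or rounding. A one-sample test of 20% against a fixed 11% also comes near (111.4, or 111.4/0.9 = about 124 per arm), but it ignores sampling error in the control arm and does not suit a two-arm chi-square comparison.

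A reader might also set the 20% against the Discussion's remark that the effect of SJZD on recurrence is not known. That is no contradiction: the 20% is labelled an estimate, and an unknown effect is the reason for a trial.

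**Conclusion.** The point holds in a limited form. The printed rates neither reproduce 240 nor define the comparison of recurrence between SJZD and placebo. Taken as the two compared proportions, they require about 562 to 564 patients, and 240 gives about 45% power. Taken as a reduction against placebo, the same 240 give anything from 15% power (20% relative reduction from 26.6%) to 98% (20-point reduction from 26.6%). The width of that range is the finding: which power applies depends on a definition and a control rate that the section does not give.

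These figures assume 108 evaluable per arm, a two-sided 5% test without continuity correction unless stated, and, for the reduction readings, control rates borrowed from the Discussion, which the protocol does not adopt as design assumptions.

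**What to change.** Keep 240 and rewrite the Sample size paragraph on the primary endpoint.

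1. Retrieve the inputs actually entered into SAS.
2. Replace the 11% and 20% effective rates with the 12-month recurrence rates assumed for placebo and for SJZD, with a source or rationale for each.
3. Name the formula, including any continuity correction and the way dropout was added.
4. Recalculate, and state the power that 108 evaluable per arm delivers. For example: about 80% power for a 14.9-point reduction from 26.6% or an 18.7-point reduction from 51.6%; 51% to 37% power for an 11-point reduction across the same control rates.

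The example differences are worked back from a fixed 240, so they describe what the trial can detect and do not replace the design assumption asked for in item 2.

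The cost is a change of protocol wording, with no extra patients. The stated power may look less favourable, particularly for an 11-point effect. If the original inputs do support 240, printing them settles the matter.

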### Data collection and registration

Data will be recorded in CRF and then entered and stored in REDcap (http://longhua.site/redcap3), a web-based electronic database. All clinical investigators will be trained on how to communicate with patients and how to collect and input information into the electronic database. A total of five visits will be conducted in this trial. Investigators will obtain the informed consent of participants, and then assess the general and demographic information, collect their biomedical and adenomatous information at baseline. They will provide participants with 3 months of drugs/placebo from enrollment to the third visit. For visit 2∼visit 4, patients will be asked to return the empty packages to confirm drug compliance. Telephone calls will be arranged every month to contact patients about their feelings, AEs and adherence to the study. Adenomatous tissue will be collected endoscopically and stored according to the regulations and requirements of the pathological department at visit 4 and visit 5. Original data and collected samples will be preserved at least 5 years after closure of the trial. An independent data monitoring committee (DMC) will be established and will include clinical epidemiologists, data monitors, and statisticians who are not involved in the trial and are independent from sponsors. No competing interest will exist. They will review the documents, check CRFs and relevant data every 6 months to monitor the safety of the study, ensure the authenticity of the profiles and protect confidentiality of participants information. DMC will give suggestions on the study design revision or trial termination.

### Statistical analysis

SAS statistical software will be used to analyze the data. The efficacy and safety of this study will be analyzed by the principle of intention-to-treat (ITT). The missing data will be filled by the method of the last observation carried forward. The measurement data will be expressed as the mean ± standard deviation or median (quartile interval) determined by whether the data are normally distributed and the variance is uniform. χ^2^ tests will be used to compare the primary and secondary endpoints between the SJZD group and the placebo group. The paired *t*-test and independent sample *t*-test will be used for intragroup comparison and intergroup comparison, respectively. Logistic regression analysis will be used for the factors affecting the recurrence rate. Interim analysis will be arranged when 50% of the sample is collected. Sub-group analyses will be determined based on characteristics of participants such as gender, body mass index or previous history of gastrointestinal diseases. *p* < 0.05 is considered statistically significant.

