**FIGURE 1 F1:**
[figure not shown]
The flowchart of the trial.

This is a multicenter, double-blinded, randomized controlled trial (RCT) of two parallel groups. A total of 240 cases will be recruited by recruitment advertisements and introductions from clinicians at outpatient or inpatient departments. Patients who meet the inclusion criteria will be informed of the possibility of participating in this study at the outpatient clinic or at admission. A face-to-face interview will be arranged to inform the patients about the purpose, interventions, examinations and follow-up procedures of this study. After informed consent acquisition, patients will be randomized to the SJZD group or placebo group at a ratio of 1:1. An intervention phase with a 12-month treatment with SJZD granules or placebo will be implemented for recruited patients. Endoscopy will be conducted at the end of the intervention phase and 1 year later. The duration of follow-up is 24 months with 5 visits, and the schedule details are listed in Table 2.

**TABLE 2 T2:** Schedule of trial.

	Period					
Study phase	Enrollment	Visit 1	Visit 2	Visit 3	Visit 4	Visit 5
		3 months of interventions	6 months of interventions	9 months of interventions	12 months of interventions	The second year after intervention
Informed consent form	**√**					
Demographic information	**√**					
Inclusion and exclusion criteria	**√**					
General information	**√**					
Vital signs	**√**	**√**	**√**	**√**	**√**	**√**
Spleen deficiency rating scale	**√**	√	√	√	√	√
Endoscopy	**√**				√	√
Histological tests*	**√**				√	√
Routine blood tests	**√**	√	√	√	√	
Routine urine test	**√**	√	√	√	√	
Routine stool test	**√**	√	√	√	√	
Liver function	**√**	√	√	√	√	
Renal function	**√**	√	√	√	√	
Electrocardiograph	**√**	√	√	√	√	
Serum and stool samples collections	**√**				√	√
Adenomatous tissue collections*	**√**				√	√
Adverse events		√	√	√	√	√
Release drugs/placebo	**√**	√	√	√		
Retrieve empty packages			√	√	√	
Drug combination	**√**	√	√	√	√	√

Notes: Patients who are detected to find recurrence of colorectal adenoma and meet the criteria of resection are undergone endoscopy. Adenomatous tissue will be collected according to the relevant regulations and histology will be confirmed by pathological experts.

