#### Withdrawal/termination criteria

Participants will be withdrawn or terminated from the trial if they meet any of the following criteria:1. Serious adverse events are reported at any time, and patients are unable to continue2. Patients who present with serious changes or complications related to the disease during the trial3. Patients who cannot comply with the instructions and follow-up procedures of this trial, leading to incomplete medical administration records, or patients who took banned drugs or other medications that may interfere with the efficacy and safety evaluation of this study4. Patients who request to be withdrawn from the trial

Besides, researchers will record the last time of drug intake and collect evaluation items of participants who discontinue or deviate from intervention protocols.

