### Randomization and blinding

Permuted block randomization, which is stratified by recruiting sites, will be used to allocate participants to the SJZD group or placebo group in a 1:1 ratio by the SAS statistical analysis system. All drugs will be sealed in identical opaque envelopes only labeled with a random code number. Participants will be enrolled by clinicians and receive an envelope in sequence. An independent statistician will finish the randomization. Clinicians, nurses, researchers and patients who participate in this trial will all be blinded to the treatment assignment. The random number and treatment assignments will be sealed and reserved by the principal investigators of this study. The blinding will not be unmasked until the trial and data analysis finish or in the event of serious AEs. Emergency letters sealed in opaque envelopes will be sent to each recruiting site. Assignment information and emergent conditions are contained in the letter. If any serious AEs occur, the emergency letter will be opened, and the corresponding patient will be withdrawn from the trial. A report of serious AEs should be submitted to the principal investigators within 24 h. The codes of treatments will be uncovered after the closure of follow-up and the specific intervention relevant to the cords will be uncovered after data analysis.

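### Safety is assigned to ITT and LOCF has no safety exception: never-dosed patients would slightly dilute AE rates, and carried-forward values can bias visit-level safety summaries in either direction

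*Protocol article*

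**What the plan says.** The Statistical analysis section sets one rule for both kinds of outcome: "The efficacy and safety of this study will be analyzed by the principle of intention-to-treat (ITT". It continues: "The missing data will be filled by the method of the last observation carried forward". Neither sentence sets safety apart, and no separate safety population is named.

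The Outcomes section defines what is affected: "Safety outcomes will comprise physical examinations, vital signs and laboratory examinations at every visit and AEs during the intervention phase". Table 2 schedules laboratory tests and ECG at enrolment and Visits 1 to 4, and vital signs at enrolment and Visits 1 to 5.

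Three other statements bear on how safety data go missing or are kept:

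- Randomization and blinding: "If any serious AEs occur, the emergency letter will be opened, and the corresponding patient will be withdrawn from the trial".
- Withdrawal/termination criteria: "researchers will record the last time of drug intake and collect evaluation items of participants who discontinue or deviate from intervention protocols".
- Data collection and registration: "Telephone calls will be arranged every month to contact patients about their feelings, AEs and adherence to the study".

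**The concern.** ITT protects the randomised comparison for efficacy. For harm it has two drawbacks. It counts people who had no exposure, and it counts a patient under the assigned arm even if the other product was taken.

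LOCF is a second, separate problem. Laboratory, vital-sign and ECG data are repeated measures, and here their missingness can be tied to harm, because a serious AE leads to withdrawal. The visits most likely to be filled in are therefore those of the patients whose later course matters most for safety. A patient withdrawn after Visit 1 could have laboratory results at Visits 2, 3 and 4 all supplied from one earlier reading.

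Safety stands beside efficacy in the Objectives section. A reader of the final tables should be able to trust that a safety rate describes treated patients and that a tabulated laboratory value was measured.

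This is not a detail left to an unseen analysis plan. The article states the rule, and a later plan with a treated-patient safety set would have to depart from it.

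**Working it through.** The plan gives no safety figure to reproduce: no AE rate, no never-dosed number and no expected laboratory change. From the Sample size section come 120 patients per arm and a 10% dropout allowance. All other inputs below are assumptions, shown over a range.

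**1. Never-dosed patients in the denominator.** Let f be the share of an arm never dosed, and suppose these patients contribute no AEs. Then:

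reported rate = rate in treated patients × (1 − f)

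With assumed treated-patient rates of 20% and 10%, and the same f in both arms:

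- f = 1%: 19.8% and 9.9%; difference 9.9 points; risk ratio 2.0
- f = 2%: 19.6% and 9.8%; difference 9.8 points; risk ratio 2.0
- f = 5%: 19.0% and 9.5%; difference 9.5 points; risk ratio 2.0

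In head counts, 3 never-dosed patients out of 120 turn a 10% rate into 0.10 × 117/120 = 9.75%, and 6 turn it into 0.10 × 114/120 = 9.5%.

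The power to detect 20% against 10% hardly moves. It is 58.0% in treated patients against 57.9% under ITT at f = 1%, and 56.2% against 55.8% at f = 5%.

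The shrinkage of the difference relies on similar shares in the two arms. If the 5% were all in the placebo arm, the difference would be 20 − 9.5 = 10.5 points, slightly wider than the true 10. Blinded, identical granules make similar shares the natural expectation.

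**2. LOCF on a laboratory mean.** Assume 10% dropout, a linear change over 12 months that is the same for dropouts and completers, and all dropouts last seen at month t. Then:

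LOCF mean shift ÷ true shift = 0.90 + 0.10 × t/12

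- last value at baseline: 90%
- at 3 months: 92.5%
- at 6 months: 95%
- at 9 months: 97.5%

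Under these assumptions LOCF understates the shift.

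**3. LOCF on an abnormality rate.** Assume a true 12-month abnormality rate of 2% in everyone and 10% dropout. Let x be the share of dropouts who were abnormal at their last reading. Then:

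LOCF rate = 0.90 × 2% + 0.10 × x

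- x = 0%: 1.8% (understated)
- x = 2%: 2.0% (unbiased)
- x = 20%: 3.8% (overstated)
- x = 50%: 6.8% (overstated)

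The sign depends on whether patients leave before harm shows or at its peak. Withdrawal after a serious AE makes the second case plausible.

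**The case against.** The strongest case against the point is that it has little practical weight.

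- **Never-dosed patients may be few.** Table 2 releases product at enrolment. It would be tempting to treat the whole 10% dropout allowance as never dosed, but the Sample size section does not equate the two, and patients who leave after starting treatment belong in both sets. This stands, which is why the range above stops at 5%; even that figure is an assumption.
- **Assigned and received product should rarely differ.** Packs are coded and identical, and no switching is planned. Only a dispensing error would separate the two. This stands; grouping by product taken is a convention with no demonstrated effect here.
- **AE counts are not shown to be imputed.** AEs are recorded as events with onset and duration, and patients are telephoned monthly about them. Nothing says that LOCF is applied to them. This stands and confines the LOCF point to visit-level laboratory, vital-sign and ECG data.
- **Data are collected from discontinuers.** If the evaluation items gathered at that point include laboratory tests (the text does not list them), the value carried forward is the one at discontinuation, possibly abnormal. This stands and removes any fixed direction from the LOCF bias.
- **Safety oversight does not rest on this analysis.** The data monitoring committee reviews data every 6 months, and nothing ties that review to ITT or LOCF. This also stands.

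None of these removes the stated rule. Safety is still assigned to ITT, and LOCF still has no limit.

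**Conclusion.** The point holds as a minor one. The article fixes an analysis rule that suits efficacy and fits safety data badly.

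Counting never-dosed patients lowers AE rates in proportion to their share. With similar shares in the arms it shrinks the risk difference by the same factor and leaves the risk ratio unchanged. At assumed shares of 1% to 5%, a 10-point difference becomes 9.9 to 9.5 points. The true share is unknown.

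LOCF can bias visit-level safety summaries either way. Under the assumptions above, the mean shift falls to between 90% and 97.5% of its true size, while a 2% abnormality rate could be reported as anything from 1.8% to 6.8%.

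A reader might infer that the plan will understate harm throughout. The documents do not support that. Only the dilution of AE rates has a predictable direction, and it is small; LOCF has no fixed direction and is not shown to touch AE records.

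**What to change.** Keep ITT for efficacy. For safety, state that the analysis set is all patients who took at least one dose, grouped by the product actually taken. Summarise AEs, laboratory tests, vital signs and ECG as observed, including the items collected at discontinuation, and state that LOCF is not used for safety data. Report the number of patients contributing at each visit.

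This needs about two sentences of analysis wording and no new data collection: last intake and discontinuation data are already planned, as are the monthly calls and the return of empty packages. The cost is that safety and efficacy tables may have slightly different denominators, which a footnote can explain.

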#### Inclusion criteria

Participants will be eligible if they meet all of the following criteria:1. Individuals aged from 18 to 75 years, regardless of gender2. Individuals who underwent complete painless endoscopic adenoma resection (excluding hot polypectomy, hot snare polypectomy and argon plasma coagulation) within 2 weeks before recruitment3. At least 1 but no more than 6 CRAs confirmed by histology (including tubular, tubulovillous, and villous adenoma)4. Boston Bowel Preparation Scale (BBPS) score ≥7 points5. The score of SDS in TCM ≥20 points6. Individuals with adequate organ function7. Individuals who provide informed consent and can cooperate with long-term follow-up

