#### Exclusion criteria

Participants will be excluded if they meet any of the following criteria:1. The adenoma was not completely removed in previous endoscopy2. Individuals who regularly take aspirin, non-steroidal anti-inflammatory drugs, cyclo-oxygenase 2 inhibitors, calcium or vitamin D and who receive long-term systemic immunotherapy3. Pregnant or lactating women4. Individuals with mental disorders or other conditions who are not able to cooperate5. Individuals who are unable to take drugs orally, lack physical integrity of the upper gastrointestinal tract, or have malabsorption syndrome and other diseases that investigators consider may interfere with gastrointestinal movement or absorption6. Individuals who are complicated with acute and chronic diseases, including severe cardiovascular, hepatic and renal diseases, or experience severe postoperative complications7. Other situations that investigators consider unsuitable for participation

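### Last observation carried forward has no valid recurrence status to carry for a patient who misses the month-12 endoscopy; read naturally, it counts that dropout as recurrence-free

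*Protocol article*

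**What the plan says.** - **Missing data (Statistical analysis).** "The missing data will be filled by the method of the last observation carried forward". No endpoint is exempted. The same section analyses efficacy by intention-to-treat, so dropouts stay in the denominator.
- **Primary endpoint (Outcomes).** "The primary outcome is the recurrence rate of CRA between the SJZD group and the placebo group at the first year after CRA removal". It is binary, and chi-square "tests will be used to compare the primary and secondary endpoints between the SJZD group and the placebo group" (Statistical analysis).
- **When it is measured (Study design and setting).** "Endoscopy will be conducted at the end of the intervention phase and 1 year later". Table 2 marks endoscopy at enrolment, visit 4 (month 12) and visit 5 only; visits 1 to 3 have none.
- **Status at entry.** Inclusion criterion 2 admits "Individuals who underwent complete painless endoscopic adenoma resection" within two weeks before recruitment. Exclusion criterion 1 removes patients for whom "The adenoma was not completely removed in previous endoscopy".
- **Expected loss (Sample size).** "Assuming that the dropout rate in each group was 10"%, which is 12 of 120 patients per arm.

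**The concern.** Carrying the last observation forward presupposes an earlier measurement of the same outcome. Here there is none between the resection and the single month-12 assessment. If the state of the colon after resection is used as the last observation, a patient who leaves the trial becomes a treatment success.

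At stake is the primary comparison. Recurrence would be understated in both arms, and any excess of dropout in one arm would appear as benefit for that arm. Some losses may be related to treatment: the Randomization and blinding section withdraws a patient whose code is opened for a serious adverse event. If that patient's month-12 endoscopy is not obtained, a withdrawal for harm would count towards efficacy.

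The year-2 endpoint has a related problem. For a patient negative at year 1 who misses the second endoscopy, the rule assumes no new adenoma, although the Discussion reports recurrence rising with longer follow-up. A patient positive at year 1 is carried forward as a recurrence.

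**Working it through.** **Step 1: what can be carried.** The plan gives no figure for the effect of its rule, so there is none to reproduce. For a patient with only the scheduled examinations who misses visit 4, there are three readings:

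1. Carry the cleared colon after resection: scored as no recurrence. This is the natural reading.
2. Carry post-baseline values only: nothing exists to carry, so the endpoint stays missing, contrary to the intention-to-treat statement.
3. Carry the pre-resection finding (1 to 6 adenomas, inclusion criterion 3): every dropout becomes a recurrence, which is not sensible after complete resection.

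None of them gives a usable primary endpoint. Steps 2 to 4 follow reading 1.

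**Step 2: formula and inputs.** With true recurrence p and dropout d unrelated to recurrence, the observed rate is p × (1 − d). There are 120 patients per arm (Sample size). p runs from 26.6% to 51.6%, the published range in the Discussion; 40% is an assumed mid-point. The test is the pooled chi-square at two-sided 0.05. Rejection rates come from exact enumeration of the two binomial counts.

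**Step 3: equal dropout of 10%.** Both rates are multiplied by 0.90, and so is their difference. Taking 51.6% versus an assumed 31.6%:
- 0.516 × 0.90 = 46.4%
- 0.316 × 0.90 = 28.4%
- the difference falls from 20 points to 18

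With no true effect both arms show the same rate, and rejection stays near 5%.

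**Step 4: unequal dropout, no true effect.** The spurious benefit is p × (d₂ − d₁), in favour of the arm with the larger d. All splits are assumed.

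| True recurrence in both arms | Dropout | Observed rates | Spurious benefit (points) | Two-sided rejection |
|---|---|---|---|---|
| 26.6% | 8% vs 12% | 24.5% vs 23.4% | 1.1 | 5.5% |
| 40% | 8% vs 12% | 36.8% vs 35.2% | 1.6 | 5.9% |
| 51.6% | 8% vs 12% | 47.5% vs 45.4% | 2.1 | 5.8% |
| 26.6% | 5% vs 15% | 25.3% vs 22.6% | 2.7 | 7.7% |
| 40% | 5% vs 15% | 38.0% vs 34.0% | 4.0 | 10.1% |
| 51.6% | 5% vs 15% | 49.0% vs 43.9% | 5.2 | 11.9% |
| 26.6% | 5% vs 20% | 25.3% vs 21.3% | 4.0 | 11.4% |
| 51.6% | 5% vs 20% | 49.0% vs 41.3% | 7.7 | 21.8% |

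**Step 5: is scoring missing as recurrence a better single rule?** The observed rate becomes p × (1 − d) + d. At 5% versus 15% dropout with no true effect:
- p = 51.6%: 54.0% versus 58.9%, rejection 11.6%
- p = 26.6%: 30.3% versus 37.6%, rejection 22.4%

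It biases in the opposite direction, by as much or more, so it can serve only as a bound.

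**The case against.** **The coding is inferred.** A reader might conclude that the plan scores every patient without a month-12 endoscopy as recurrence-free. The article does not say so. Recurrence has no baseline value as such, a rule confined to post-baseline values would carry nothing, and an adenoma found at an unscheduled earlier endoscopy would be carried forward as recurrence. This stands, and it limits the point to patients with only the scheduled examinations and to the natural reading. It does not rescue the rule, because the other readings fail too.

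**The type I error harm is conditional.** A reader might also infer that the rule inflates type I error in this trial as planned. The documents do not support that. The Sample size section assumes the same dropout in each arm, and the trial is double-blind with a placebo matched in appearance, smell and taste. With equal dropout the effect is diluted, which works against the tested treatment. A modest imbalance of 8% versus 12% adds less than one percentage point to the 5% level. This stands; the larger figures depend on larger imbalances that nothing in the article predicts.

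**Stopping treatment need not mean missing data.** The Withdrawal/termination criteria say that evaluation items will be collected from participants who discontinue or deviate. This is a partial mitigation, but the article does not promise that a month-12 endoscopy is among those items.

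**Could this be left to the analysis plan?** Details of imputation could. Here, however, the protocol states the rule itself, and the stated rule is unsuitable.

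**Conclusion.** The concern holds in a limited form. The plan fixes a missing-data rule that has nothing valid to carry for the primary endpoint in a patient with only the scheduled endoscopies. Its natural reading turns dropout into success. For year 2 it assumes that patients negative at year 1 who miss the second endoscopy stay negative.

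Under the plan's own equal 10% dropout, the consequence is dilution by a tenth with type I error near 5%. If dropout is unequal, the arm with more dropout gains. At an assumed 5% versus 15%, the false-positive rate is 7.7% to 11.9% over the recurrence range in the Discussion; at 5% versus 20% it is 11.4% to 21.8%; at 8% versus 12% it is about 5.5% to 5.9%.

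These figures assume 120 per arm, dropout unrelated to true recurrence and reading 1 of the rule. The dropout splits and the 31.6% and 40% rates are assumptions.

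**What to change.** In the Statistical analysis section, remove last observation carried forward for the month-12 and month-24 recurrence endpoints. Replace it with multiple imputation of missing recurrence status, done by arm from baseline data already collected. State that any endoscopy result obtained from patients who discontinue treatment will be used.

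Add a tipping-point sensitivity analysis that varies the assumed recurrence among missing patients in each arm. Scoring all missing patients as recurrences may be shown as an extreme bound only. The choice of imputation variables can be left to the statistical analysis plan, fixed before unblinding.

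The cost is a change of wording, a little more analysis and slightly wider confidence intervals. No extra visits or data are needed.
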